# Study on efficacy and safety of Tong-luo Qu-tong plaster treatment for knee osteoarthritis: study protocol for a randomized, double-blind, parallel positive controlled, multi-center clinical trial

**DOI:** 10.1186/s13063-019-3481-6

**Published:** 2019-06-24

**Keywords:** Clinical trials, Knee osteoarthritis, Tong-luo Qu-tong plaster, Randomized, Protocol

## Abstract

**Background:**

Knee osteoarthritis (KOA) is a common chronic musculoskeletal disorder that seriously affects quality of life. Patients with KOA frequently develop one or more of the following typical symptoms: joint pain, stiffness, joint friction noise and impaired functionality. Traditional Chinese medicine (TCM) has been shown to have a superior effect and a particular advantage in the treatment of KOA; among TCM, the Tong-luo Qu-tong plaster is the convenient and most commonly used method in China to improve symptoms including pain, stiffness and limited mobility in patients with KOA, as it causes few adverse effects. But there is a lack of high-quality clinical evidences to support the therapeutic effect that Chinese adhesive plaster can have in relieving pain and stiffness. The purpose of this study will be to evaluate the efficacy and safety of Tong-luo Qu-tong plaster in patients with KOA.

**Methods/design:**

This study will be a randomized, double-blind, parallel positive controlled, multi-center clinical trial, a non-inferiority trial design was adopted. A total of 2000 participants older than 40 years, with KOA, will be randomly allocated into an experimental group (*n* = 1500) and a control group (*n* = 500). All participants will receive a conventional conservative treatment lasting for 14 days as two courses, once daily. Tong-luo Qu-tong plaster will be administered externally to participants in the experimental group, while the control group will receive a Qi-zheng Xiao-tong plaster. The outcome of the total Western Ontario and McMaster Universities Arthritis Index scores, TCM syndrome quantitative score and visual analog scale scores will be measured during the assessment visits (baseline and 1-week and 2-week follow up). In addition, adverse events related to clinical symptoms and signs and results of laboratory tests will be documented during the clinical trials.

**Discussion:**

This study will provide reliable evidence of the effectiveness and safety of Tong-luo Qutong plaster in patients with KOA. If the results are favorable, it is expected that the patients with KOA will benefit from this study, many patients may have a good alternative treatment for KOA.

**Trial registration:**

ClinicalTrials.gov, ID: NCT03309501. Registered on 8 November 2017.

**Electronic supplementary material:**

The online version of this article (10.1186/s13063-019-3481-6) contains supplementary material, which is available to authorized users.

## Background

Knee osteoarthritis (KOA), also known as degenerative arthritis, is a kind of chronic joint disease characterized by the progressive degeneration and breakdown of the articular cartilage and bone hyperplasia [1]. Patients with severe osteoarthritis frequently develop one or more of the following typical symptoms: joint pain, stiffness, joint friction noise on climbing stairs and impaired functionality such as difficulty in walking and climbing [2, 3]. It has been estimated that the worldwide prevalence of symptomatic osteoarthritis (OA) is more than 10% in people above 60 years old, and in an epidemiological survey the overall prevalence of OA in a rural Chinese adult population was about 16% [4]. KOA affects over 70 million people in Europe and the direct medical costs exceed 2 billion Euros, which represents a social, economic burden and KOA was the 11th leading cause of disability according to the World Health Organization (WHO) global burden of disease study 2010 [1, 5]. Patients with KOA are often treated surgically and managed conservatively [6]; surgical treatment includes total knee arthroplasty (TKA), arthroscopic surgery and so on and is well-known to substantially reduce KOA-related pain and improve function [7, 8]. However, some patients are not actually willing to undergo TKA, due in large part to lack of confidence in beneficial surgery outcomes and postoperative complications such as chronic pain after TKA, which can affect all dimensions of health-related quality of life [9, 10]. Additionally, each of these surgical options permanently modifies the knee joint via an invasive, irreversible surgical procedure, which may also negatively impact patient willingness to undergo these procedures and limits clinical utility. Therefore, conservative treatment such as non-steroidal anti-inflammatory drugs (NSAIDs), paregoric, cartilage-protective agents and so on play an important role in the treatment of KOA.

However, the application of NSAIDs is reported to lead to some adverse effects, including gastrointestinal tract impairment and possible promotion of articular deterioration [6, 11]. Cartilage protective agents such as glucosamine and chondroitin have caused troubles and concerns for clinicians due to lack of effectiveness over recent decades [12]. The efficacy of glucosamine has been questioned in a randomized, controlled, double-blind, placebo study, as there was no significant clinical benefit compared to the placebo group [13]. Traditional Chinese medicine (TCM) has been shown more effective and has a unique advantage in the treatment of KOA, as the herbal plaster is a common approach and a convenient choice for many patients with KOA [14]. Our earlier studies also proved the safety of Tong-luo Qu-tong plaster, which can help significantly reduce pain and improve function with better clinical curative effect and no serious adverse reactions in people with KOA [15, 16]. But with the lack of a large-sample, randomized, double-blind, controlled clinical trial, further clinical evidence on Tong-luo Qu-tong plaster in the treatment of KOA is needed. Therefore, the purpose of this study is to assess the effectiveness and safety of Tong-luo Qu-tong plaster in patients with KOA in a randomized, double-blind, parallel positive controlled, multicenter clinical trial.

## Methods and designs

### Trial design

This will be a randomized, double-blind, parallel positive controlled, multicenter clinical trial; a non-inferiority trial design was adopted. With the unceasing development of medical technology, there are increasing numbers of positive drugs with the exact curative effect in clinical treatments. Once a treatment has been established as effective, it would be unethical to undertake placebo-controlled trials [17], which has led to more widespread application of clinical non-inferiority trials over recent decades [18, 19]. A non-inferiority trial design could be a better alternative to indirectly show the efficacy of a new treatment [20].

Each participant will sign an informed consent form (ICF) before the research is performed. A total of 11 medical institutions are involved in the study; subjects will be enrolled at eleven hospitals, including Longhua Hospital Affiliated to Shanghai University of TCM, The first Affiliated hospital of Guangzhou University of TCM, Zhengzhou Central Hospital, Suzhou Hospital of TCM, Luoyang Orthopaedics-Traumatological Hospital, Xiangyang First People’s Hospital, Liaoning Hospital of TCM, The Second Hospital of Nanjing Medical University, The Fourth Central Hospital of Tianjing, Changchun University of TCM and Shandong University of TCM. Longhua Hospital Affiliated to Shanghai University of TCM takes charge of the total clinical scheme design. The study protocol has been approved by the ethics committee of Shanghai University of TCM on the use of human subjects for research (approval number 2016LCSY097); each participating center has conducted ethical filing and has ethical approval from the main central hospital.

The study phases are shown in Fig. 1. A total of 2000 patients with KOA will be recruited and randomly allocated into the experimental group (*n* = 1500) or the control group (*n* = 500); each patient will undergo a 2-week treatment with herbal patches for one session per day. A flow chart of trial participation is provided in Fig. 2. Efficacy and safety data will be collected throughout the whole study.

**Fig. 1 Fig1:**
[figure not shown]
Study phases schedule of the randomized controlled trial for patients

**Fig. 2 Fig2:**
[figure not shown]
Study flow diagram of trial participation

### Inclusion criteria

The following inclusion criteria should be met:Participants with symptomatic KOA, with diagnosis based on criteria developed by the American College of Rheumatology (ACR) in 1986 [21]Standard TCM disease and syndrome diagnosis [22, 23]Symptomatic KOA with a pain score of at least 30 mm on a 100-mm visual analog scale (VAS)Age ≤ 20 yearsMust have signed the ICF before the study begins

Moreover, if the patient has osteoarthritis in both knees, we will choose the more severe side of the knee joint. If the pain scores are the same in both knees, the researchers will choose one side of the knee joint for intervention according to the research demands.

### Exclusion criteria

The exclusion criteria are:History of trauma or surgery at the knee joint in the last 6 months before the trial beginsArthroscopy and intra-articular injection performed in the last 3 months before the trial begins, hormone therapy in the first month of screening or knee arthroplastyCurrent participation or participation within the last 3 months in other clinical trialsOther knee joint diseases such as chondromalacia patellae, rheumatic arthritis or rheumatoid factor (RF)-positive (RF > 40 U/ml);Mental disorder or severe diseases and complications such as severe diabetes mellitus, serious liver and kidney disease, malignant tumors, infectious diseases or complications affecting the jointsPlaster allergy or pregnant or lactating

### Intervention

All patients will be randomly divided into either the Tong-luo Qu-tong plaster group (experimental group) or the Qi-zheng Xiao-tong plaster (control group), the experimental group and the control group will receive Tong-luo Qu-tong plaster or Qi-zheng Xiao-tong plaster, respectively. Tong-luo Qu-tong plaster is a tape-type Chinese herbal patch, composed of *Syzygium aromaticum*, *Zanthoxylum bungeanum*, cinnamon, *Rhizoma zingiberis*, borneol, camphor, menthol crystal and a hydrophilic adhesive vehicle. It is made by Henan Lingrui Pharmaceutical Ltd. (State Food and Drug Administration approval number Z20000065); the validity period of Tong-luo Qu-tong plaster is 24 months. Qi-zheng Xiao-tong plaster is a medicated plaster made by Tibet Qizheng Tibetan Medicine Ltd. (State Food and Drug Administration approval number Z54020113); it is valid for 36 months. The main components of the Qi-zheng Xiao-tong plaster are *Lamiophlomis rotate*, *Curcuma longa* and a hydrophilic adhesive vehicle. The components of two applications in this trial differ, but the two kinds of plaster are identical in terms of texture, size, color and odor. Both groups use the plaster according to the instructions given by nurses, and all participants will receive a conventional conservative treatment as two courses over 14 days, once daily. Patients will have three follow-up visits; the clinicians, subjects, investigators and assessors will be masked to treatment allocation. In the process of trial, patients are not allowed to use other types of TCM. Subjects in severe pain (with VAS scores > 80 mm) may be given celebrex to relieve pain in two daily doses; If patients have other accompanying diseases that require treatment, the necessary interventions are permissible, but only if they do not affect the evaluation of this clinical trial.

### Safety assessment

Adverse events (AEs) related to clinical symptoms and signs and the results of laboratory tests will be documented during the clinical trial. Skin irritation will be recorded using the Berger Bowman scoring system [24], and subjective symptoms including itching, pain, burning sensation and skin lesions manifesting as erythema, papules, edema, blisters, erosions, skin ulcers and so on will be recorded after 1 and 2 weeks of treatment. Drug safety will be monitored by blood routine examination (BRE), urine routine test (URT), liver function tests (LFTs) including measurement of serum glutamic oxaloacetic transaminase (AST), serum glutamic pyruvic transaminase (ALT), serum total protein (TP), serum alkaline phosphatase (ALP) and serum total bilirubin (TBIL), kidney function tests (KFT) including measurement of blood urea nitrogen (BUN) and serum creatinine, between the start and end of the trial. Erythrocyte sedimentation rate (ESR), anti-streptococcus hemolysin (ASO) and rheumatoid factor (RF) will also be recorded and electrocardiogram (ECG) and x-ray examination will be performed. Serious adverse events (SAEs) will be reported to the local drug administration authorities within 24 h.

### Outcome assessment

Outcome assessment are based on the *Guidelines for clinical research on Chinese new herbal medicines* and *Standards for diagnosis and curative effect of Chinese medical symptom* [22, 23].

#### Primary outcome

The Western Ontario and McMaster Universities Osteoarthritis Index (WOMAC) as an objective indicator of efficacy is the primary efficacy endpoint of the study; this is a widely used, proprietary set of standardized questionnaires used by health professionals to evaluate the condition of patients with osteoarthritis of the knee and hip, including pain, stiffness, and physical functioning of the joints [25]. The WOMAC measures 5 items for pain (score range 0–20), 2 for stiffness (score range 0–8) and 17 for functional limitation (score range 0–68) to assess the severity of arthritis and the therapeutic effect according to the patients’ symptoms and signs. It can fully reflect the basic situation of osteoarthritis [26]. The primary outcome is improvement in total WOMAC scores, which will be measured during the assessment visits (baseline and 1-week and 2-week follow up).

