#### Secondary outcome assessment

The secondary outcome is change between baseline and the end of treatment in the TCM syndrome quantitative score [23], VAS scores [27] and time of onset of pain relief after administration of the drug. The VAS scores range from 0 mm to 100 mm, and it is widely used for clinical evaluation of the degree of pain. The time when the VAS score was reduced by at least 10 mm for the first time after administration of the drug was recorded, namely the time of onset of pain relief.

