### Sample size estimation

Our study was designed as a non-inferiority trial and sample size calculations are based on the primary outcome measurement. First, the minimal clinically important difference in WOMAC scales in KOA is estimated from previous studies [28] as 15.50 points. Second, we assume that based on previous literature [29], the square deviation of the WOMAC score is 318.88. For power of 80% and an alpha value of 2.5% (two-tailed), the sample size is calculated using the following formula:$$ n=\frac{\frac{4}{3}{\left({u}_{\upalpha}+{u}_{\beta}\right)}^2{\upsigma}^2}{{\left(\varDelta -\updelta \right)}^2}\ \left({u}_{\upalpha}=1.6449,\kern0.5em {u}_{\beta }=1.2816\right) $$

Thus, we obtained the sample size of 1600 patients for this trial; allowing for a conservative 20% dropout rate, the total sample size was set at 2000 patients (1500 in the Tong-luo Qu-tong plaster group).

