### Statistical analysis

The statisticians and the main researchers are responsible for the statistical analysis plan. We will analyze all data with SAS 9.2 statistical software. Data sets including the full analysis set (FAS), per-protocol set (PPS) and safety set (SS), will be analyzed in terms of actual subjects, shedding cases, excluding cases, demographic and characteristics of cases, and efficacy and safety analyses will be conducted according to the intention-to-treat (ITT) principle.

Categorical data presented as frequency tables or percentages and continuous data presented as mean ± standard deviation, median, superior and inferior quartiles, minimum value and maximum value will be used to describe the characteristics of patients in both groups. The primary outcome will be compared in the two groups; categorical data will be analyzed by chi-squared test or Fisher’s exact test, and continuous data with a normal distribution will be analyzed by the *t* test or variance testing. If the data are not normally distributed or do not satisfy homogeneity of variance, they will be analyzed using the Wilcoxon rank sum test or Wilcoxon symbols test to compare the two treatment arms. A two-sided *P* value ≤0.05 or ≤0.01 will be considered statistically significant.

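### The protocol does not name the visit, week 1 or week 2, that carries the primary WOMAC non-inferiority comparison

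*Protocol article*

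**What the plan says.** Protocol article, Primary outcome: the outcome is improvement in total WOMAC, "which will be measured during the assessment visits (baseline and 1-week and 2-week follow up"). The methods paragraph of the Abstract gives the same visit schedule and singles out neither visit.

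Secondary outcome assessment: "The secondary outcome is change between baseline and the end of treatment in the TCM syndrome quantitative score", with VAS and time to onset of pain relief listed alongside. Under Trial design, "each patient will undergo a 2-week treatment with herbal patches for one session per day", so the week 2 visit is the end of treatment and week 1 falls midway.

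Sample size estimation: "Our study was designed as a non-inferiority trial and sample size calculations are based on the primary outcome measurement". The formula there is for one two-group comparison of means, and no visit is attached to it. The level is given as "For power of 80% and an alpha value of 2.5% (two-tailed").

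Statistical analysis: "The primary outcome will be compared in the two groups". The tests offered are the t test or variance testing, with Wilcoxon tests as the fallback. No visit, combination of visits or baseline adjustment is mentioned.

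**The concern.** The time point is part of what a primary outcome is. Here the outcome has two post-baseline readings, while the sample size and the analysis treat it as a single quantity. The article fixes an end point in time for the secondary outcomes but not for the one that decides the trial.

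Two things are at stake. First, with the visit open, an analyst who has seen the data could report whichever visit meets the margin. Second, if that freedom were used so that either visit could deliver the claim, the chance of wrongly declaring non-inferiority would be higher than for a single test at the chosen level.

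**Working it through.** **Which level is planned?** The article gives no single answer:

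- Sample size text: 2.5% two-tailed, which is one-sided 1.25%.
- Sample size formula: a quantile of 1.6449, which is one-sided 5% (upper tail area 0.0500).
- Statistical analysis: two-sided 0.05 or 0.01. The first corresponds to one-sided 2.5%.

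I therefore show three one-sided levels and take 2.5% as the reference.

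**The plan's own figure.** The dropout step reproduces: 1600 / 0.8 = 2000. The 1600 does not. With Δ − δ taken as 15.50 (an assumption, since δ is not given), the printed formula gives (4/3) × (1.6449 + 1.2816)² × 318.88 / 15.50² = 15.2 for the control arm, or about 61 in total at 3:1 before rounding up. That is a separate problem. It matters here only in that the formula contains one comparison and no allowance for two visits.

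**Error rate if either visit could count.** Let Z₁ and Z₂ be the week 1 and week 2 test statistics, with correlation r. Take the true difference to lie exactly at the margin at both visits. With critical value c at one-sided level α:

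P(claim at either visit) = 1 − P(Z₁ < c, Z₂ < c), bivariate normal.

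For r = 0 this is 1 − (1 − α)². At α = 0.025 that is 1 − 0.975² = 0.0494. The Bonferroni bound is 2 × 0.025 = 0.05. The values of r are assumptions, because the article gives no correlation.

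| One-sided level per visit | r = 0 | r = 0.5 | r = 0.7 | r = 0.8 | r = 0.9 |
|---|---|---|---|---|---|
| 0.0125 | 0.0248 | 0.0232 | 0.0215 | 0.0201 | 0.0181 |
| 0.025 | 0.0494 | 0.0454 | 0.0417 | 0.0390 | 0.0352 |
| 0.05 | 0.0975 | 0.0878 | 0.0804 | 0.0752 | 0.0681 |

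**Error rate under the other possible rules.**

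- Week 2 alone: one test, so the error is α.
- One longitudinal contrast: one test, so the error is α.
- Both visits must succeed: the error cannot exceed α. With the difference at the margin at both visits it is 2α minus the table entry. At α = 0.025 and r = 0.5 that is 0.05 − 0.0454 = 0.0046.

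Only the either-visit rule inflates the error.

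**The case against.** The strongest reply is that the sentence in Primary outcome is a measurement schedule and not a testing rule. The Abstract uses the same schedule wording for WOMAC, the TCM syndrome score and VAS together, yet Secondary outcome assessment evaluates the last two only at the end of treatment. Listing both visits is thus compatible with a single week 2 comparison, and week 2 is the natural reading. This stands as far as it goes: a reader might infer that both visits are tested and either suffices, so that the error rate does exceed the planned level, but the article says neither. It also has no single planned level to exceed. At the 2.5% two-tailed level stated in words, even an either-visit rule stays at or below about 2.5% one-sided.

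A reader might also infer that week 1, being mid-treatment, shows a smaller difference between arms and so favours non-inferiority. Nothing in the article supports that. Time to onset of pain relief is itself an outcome, and a slower-acting plaster could look worse at week 1 and catch up by week 2.

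Finally, a multiplicity rule, or what to do if the visits disagree, may sit in the analysis plan, which is not shown. Their absence is not held against the article. The reply does not cover the definition of the primary outcome itself: its time point belongs in the protocol, and the article found room to give one for the secondary outcomes.

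**Conclusion.** The point holds in a conditional form. The visit for the primary WOMAC comparison is not named in the outcome definition, the sample size section or the analysis section, so the confirmatory test is not tied to one result. If success at either visit could count, one-sided 2.5% would become about 3.5% to 4.9%. This rests on an assumed correlation of 0.9 to 0 and a true difference at the margin at both visits. Under any of the other three rules there is no inflation. The article does not establish that the error rate is inflated, nor that week 1 is biased towards success. What it does establish is an ambiguity in the primary endpoint that should be closed before unblinding.

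**What to change.** In Primary outcome, state that the single primary comparison is the between-group difference in change in total WOMAC from baseline to week 2 (end of treatment), and that week 1 is a secondary time point. Repeat the visit in the sample size and analysis sections.

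In Statistical analysis, replace the unadjusted t or rank test for this outcome with a baseline-adjusted repeated-measures model that includes both post-baseline visits, and take the week 2 treatment difference from it. Week 1 then informs the week 2 estimate for participants whose week 2 value is missing. This is relevant because the plan allows for 20% dropout (0.20 × 2000 = 400 participants), though how many of them would have a week 1 value is not known.

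Naming the visit takes one sentence and cures the ambiguity. The model takes a short paragraph and uses data already scheduled for collection, so no added visits or participants are needed. Both changes should be dated before unblinding.
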